### Statistical analysis

To describe the sociodemographic characteristics of the patients in the two groups, absolute and relative frequencies (%) will be used for the qualitative variables, and the mean and standard deviation will be used for the only quantitative variable (age) if it presents a normal distribution according to the Shapiro–Wilk test. In case of presenting a non-normal distribution, the median and the interquartile range will be computed.

To compare the sociodemographic characteristics between the groups, the chi-square or Fisher’s exact test will be used for the qualitative variables, and the student’s t-test or the Mann–Whitney U test will be computed for the quantitative variable.

For all patients and at each follow-up moments, the difference between the frequency of each suicidal behavior and the baseline frequency will be calculated. Then it will be evaluated if these differences follow a normal distribution (Shapiro–Wilk test). In this case, the mean differences for each behavior between both groups will be compared using the t-Student test. Otherwise, the medians will be compared with the Mann–Whitney U test. The *p*-values obtained will be corrected according to the Bonferroni criterion.

To assess whether the change in emotional regulation mediates the change in the frequencies of each suicidal behavior, the difference between the value of the DERS scale at the last follow-up and the baseline will be calculated, and the Sobel test will be used on a regression model whose dependent variable will be the difference in the frequency of each behavior and the independent variable will be the treatment. Previously, the probability distribution of the quantitative variables will be evaluated and it will be considered whether it is necessary to carry out any transformation of data to guarantee compliance with the assumptions of the regression model.

Both for the frequencies of the different suicidal behaviors and for the DERS scale, the missing values will be imputed according with the multiple imputation method using chained equations (MICE) with appropriate models for each variable to be imputed, considering sociodemographic characteristics, the hospital of recruitment and the baseline measurements of frequencies and DERS scale as independent variables.

Regarding acceptability, the UEQ Data Analysis Tool offers a benchmark to classify the application in 5 categories of 6 scales: excellent, good, above average, below average and bad allowing conclusions to be drawn about the relative quality of CALMA compared to other products.^2^

To evaluate and compare the time to readmission in patients enrolled during hospitalization, a Cox regression model will be adjusted, considering the treatment of each patient as the independent variable. For this, the time elapsed from study entry to readmission (event) or to loss of follow-up or final of the study (censoring) will be calculated. In all cases, a value of *p* less than 0.05 will be considered significant. Statistical analysis will be performed with RStudio 1.4.1106.

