### Specific objectives

#### Primary specific objectives

Compare the change in the frequency of self-injurious behaviors in the participants who receive the app with the frequency in those who do not receive the application.

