## Methods and analysis

### Trial design

This protocol describes the methodology of a parallel-group, two-arm randomized controlled trial, which will employ an intervention condition (CALMA app) and a control condition (Treatment as usual-TAU) with a 3-month follow-up for each participant. Participants will be assessed at four timepoints: day-0 (baseline), day-30, day-60, and day-90.

The intervention group will receive the CALMA app and continue with the usual treatment in a public hospital mental health service. The CALMA app will be downloaded with the assistance of a team member into the participant’s smartphone during the first interview. In each follow-up interview (30-days and 60-days), the use of the app will be reinforced. The control group (TAU) will not receive the app but will keep doing the usual treatment provided in public hospitals throughout the study. The usual treatment in public hospitals in Argentina consists of a weekly visit to a psychologist and a monthly visit to a psychiatrist (in case the patient receives any pharmacological treatment). In the public hospitals of Argentina, there are no DBT programs, and most of the interventions are psychoanalytic.

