### Sample size

The sample size was calculated using the G*Power 3.1.9.4 statistical software according to the main objective. Considering a confidence level of 95%, a power of 80% and an effect size *d* = 0.85, 25 individuals per group are needed to detect a significant difference in the median frequency of self-injurious behaviors with the two tailed Mann–Whitney U test. Assuming a proportion of lost in the follow-up of 15%, then the study would have to start with 29 individuals per group.

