### Randomization

To perform the simple randomization of the treatments, the RStudio software version 1.4.1106 was used. For each of the hospitals, a patient ID vector was created (45 rows). Then, the ID of each hospital was randomly assigned a treatment, generated from a Bernoulli distribution with *p* = 0.5. Previously, a starting seed was set to ensure the reproducibility of the algorithm. The lists obtained were exported to a spreadsheet in Microsoft Excel. Each responsible investigator in each hospital received the list of the randomization sequence by email from the study coordinator ([name]).

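### The behaviour counts are tested visit by visit with Bonferroni; no planned analysis combines days 30, 60 and 90 and no visit is primary, though the trial is sized on one comparison

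*Protocol article*

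**What the plan says.** The primary objective is stated as "Compare the change in the frequency of self-injurious behaviors in the participants who receive the app", against those who do not. It names no visit and no period. The Trial design section sets assessments at baseline and days 30, 60 and 90, "with a 3-month follow-up for each participant". The SITBI is given at all of them.

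The Statistical analysis section fixes the comparison: "at each follow-up moments, the difference between the frequency of each suicidal behavior and the baseline frequency will be calculated". The arms are then compared behaviour by behaviour, with a t-test if the differences look normal and a Mann–Whitney test otherwise. The p-values are Bonferroni-corrected; the number of tests is not given.

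The Sample size section describes one comparison, made by a two-sided Mann–Whitney test: "25 individuals per group are needed to detect a significant difference in the median frequency of self-injurious behaviors". Its inputs are introduced by "Considering a confidence level of 95%, a power of 80% and an effect size", where d is set at 0.85.

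Nothing else in the analysis text pools the counts over visits. The Cox model spans follow-up, but it concerns readmission of participants enrolled as inpatients. The mediation regression uses a difference in frequency together with the DERS change at the last follow-up.

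**The concern.** Each participant contributes three follow-up frequencies under the same allocation. The plan subtracts the same baseline value from each and tests each difference separately. Two things follow.

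- **No single answer to the primary objective.** Each behaviour yields three results, and there is no rule for reading, for example, a difference at day 60 only.
- **Extra visits cost per-test power.** The trial is sized for one test at 0.05 but runs at least three corrected tests per behaviour. Combined in one analysis, the same visits would add precision.

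This is a stated analysis choice, not a detail left for an analysis plan.

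**Working it through.** **Inputs from the article:** two-sided alpha 0.05, power 0.80, d = 0.85, 25 per group before dropout, Mann–Whitney test, three follow-up visits.

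**Assumed, because the article gives no figure:** d is in SD units of a single-visit change score; data are normal; variances are equal; one correlation r holds between all four assessments, with r from 0.3 to 0.7.

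**1. The plan's own figure.** Noncentral t with Mann–Whitney efficiency 3/π = 0.955 needs 24 per group; the minimum efficiency of 0.864 needs 27. The stated 25 lies between them. Power at 25 is 0.82 (efficiency 0.955). So the sample size is reproduced for one uncorrected comparison.

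**2. Power at any one given visit under Bonferroni** (25 per arm, efficiency 0.955):
- 3 visits, alpha 0.05/3 = 0.0167: 0.67
- 3 behaviours × 3 visits, alpha 0.05/9 = 0.0056: 0.52
- 5 SITBI modules × 3 visits, alpha 0.05/15 = 0.0033: 0.45

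**3. Effect size after combining visits, constant effect.**
- Variance of a single-visit change: 2(1−r).
- Variance of the mean of three visits minus baseline: (4/3)(1−r). The ratio is 1.5, so d = 0.85 × √1.5 = 1.04, and power at 25 per arm is 0.94.
- Variance of mean follow-up adjusted for baseline: (1+2r)/3 − r² = (1−r)(1+3r)/3. So d = 0.85 × √(6/(1+3r)) = 1.51, 1.32 and 1.18 at r = 0.3, 0.5 and 0.7.
- Baseline-adjusted day 90 alone has variance 1−r², so d = 0.85 × √(2/(1+r)) = 1.05, 0.98 and 0.92. Part of the gain therefore comes from baseline adjustment and the rest from pooling.

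**4. Like-for-like power by simulation** (25 per arm, r = 0.3 to 0.7). The plan counts as successful if any of three visits passes 0.05/3. Build-up means 1/3, 2/3 and all of d = 0.85 at the three visits.

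| Effect pattern | Any of three visits, Bonferroni | Day 90 change alone, 0.05 | Mean change, one test | Baseline-adjusted mean, one test |
|---|---|---|---|---|
| Constant | 0.88–0.89 | 0.81–0.82 | 0.94 | 0.98–1.00 |
| Linear build-up | 0.70–0.72 | 0.81 | 0.64 | 0.78–0.93 |
| Month 3 only | about 0.67 | 0.81 | 0.20 | about 0.3–0.4 |

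**5. Other correlations.** A common r fixes the correlation between change scores at 0.5. Letting that correlation range from 0.3 to 0.9 with a constant effect, simulated power is 0.97 down to 0.85 for the mean change, against 0.92 down to 0.77 for any-visit testing. The combined test was better at every value tried.

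**The case against.** Visit-wise testing with Bonferroni control is valid. It uses every visit, and no bias or error inflation follows from it. A reader might infer that the repeated measurements are wasted; they are not, since each is tested. They are only never combined.

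A reader might also infer that the objective asks for a 90-day effect. It does not say so: it names no period, and the Trial design section gives a follow-up length, not a target of estimation.

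It is tempting to quote a gain from 0.82 to 0.94, but that sets one uncorrected visit against the pooled test. Against the plan as written, the gain from pooling change scores is about 5 points.

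The strongest objection is that a late or growing effect is plausible here: the app is meant to teach skills, and its use is reinforced at days 30 and 60. Averaging change scores then loses power, and choosing between an average and a late effect is a preference about the target. This stands for pooled change scores, and for any pooled analysis if the effect appears in month 3 alone. It does not stand against a baseline-adjusted average under a linear build-up, which beats any-visit testing. Nor does it excuse leaving the target unnamed. Naming day 90 would also give a single answer.

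Finally, count models may be unstable for rare behaviours with 25 per arm. This is fair and shapes the fix.

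**Conclusion.** The point holds in this form: the visits are used but never pooled, no visit is primary, and the sample size assumes one comparison where the plan makes several. The primary objective therefore has three answers per behaviour, with avoidable loss of precision. It should be changed, but it does not invalidate the plan.

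Under a constant d = 0.85 and 25 per arm, power rises from about 0.89 to 0.94 with pooled change scores and to about 0.99 with baseline adjustment. Under a linear build-up only the baseline-adjusted form gains. Under an effect confined to month 3, both pooled forms lose clearly.

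These sizes rest on normal data and assumed correlations; real self-injury counts will be skewed. Treating the three frequencies as consecutive monthly counts is also an assumption, because the article gives no recall window for the follow-up SITBI.

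**What to change.** For the primary behaviour outcome, pre-specify one baseline-adjusted analysis of all three follow-up counts. Two forms would serve:
- a negative binomial GEE or mixed model with arm, visit and baseline count;
- a baseline-adjusted comparison of the mean follow-up count after the planned multiple imputation, preferred for rare behaviours where a count model may not be stable.

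Test the average arm effect over follow-up once. Report visit-specific contrasts with intervals as descriptive. If the second form is used, add the other follow-up counts to the imputation predictors, since only baseline variables are listed now. State the recall window of the follow-up SITBI.

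If the sponsor's target is a late effect, name day 90 as the single primary contrast from the same model instead, and decide this before outcome data are seen.

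The cost is analysis wording only: no new visits, data or participants. The downside to accept is the low power of the average (about 0.2 to 0.4) if the effect appears only in month 3, against about 0.67 for any-visit testing and 0.81 for a single day-90 test.

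### The primary comparison tests raw change from baseline with no covariate, by a test chosen after a normality check; one prespecified baseline-adjusted analysis would be more precise at no data cost

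*Protocol article*

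**What the plan says.** All of this is in the Protocol article.

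- **Outcome scale (Statistical analysis).** At every follow-up, "the difference between the frequency of each suicidal behavior and the baseline frequency will be calculated".
- **Choice of test.** "Then it will be evaluated if these differences follow a normal distribution", by Shapiro–Wilk. If they do, "the mean differences for each behavior between both groups will be compared using the t-Student test". The fallback for changes that fail this check is given as follows: "Otherwise, the medians will be compared with the Mann–Whitney U test".
- **Multiplicity.** The p-"values obtained will be corrected according to the Bonferroni criterion". The number of tests is not stated.
- **Covariates.** None enters the comparison of arms. The imputation models in the same section do use "the hospital of recruitment and the baseline measurements of frequencies and DERS scale as independent variables".
- **Randomization.** "For each of the hospitals, a patient ID vector was created", and each allocation was "generated from a Bernoulli distribution with" p = 0.5, without blocks.
- **Sample size.** 25 per group for a two-tailed Mann–Whitney test at d = 0.85, 95% confidence and 80% power, raised to 29 for 15% loss.

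**The concern.** Monthly counts of self-injurious behaviour are likely to be skewed, so raw differences are dominated by a few participants with high baseline counts. Subtracting baseline fixes its coefficient at 1. The best linear adjustment uses the regression slope of follow-up on baseline, which equals ρ when the two variances are equal and is then below 1. Eligibility requires a recent episode, so regression toward the mean is likely. It affects both arms alike and does not bias the comparison, but it is a reason to condition on baseline rather than subtract it. Simple randomisation of a small sample also leaves chance baseline imbalance, which a change score handles inefficiently.

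Separately, the normality check lets the data decide whether a result is a difference in means or a rank comparison, and the answer may differ between behaviours and visits. What is at stake is power and a single interpretable effect estimate for the primary objective.

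**Working it through.** **1. The plan's own figure.** Noncentral-t power with the asymptotic relative efficiency (ARE) correction for Mann–Whitney, d = 0.85, two-sided α = 0.05:

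- ARE 3/π (normal parent): 24 per group for 80% power.
- ARE 0.864 (minimum): 27 per group.
- At the stated 25, power is 0.82 or 0.78 respectively.

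The stated 25 is reproduced within two participants. The SD to which d refers is not given.

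**2. Change score against ANCOVA, analytically.** Assume equal variance σ² at baseline and follow-up, and correlation ρ.

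- Change score: 2σ²(1−ρ).
- ANCOVA: σ²(1−ρ²).
- Ratio: (1−ρ²)/[2(1−ρ)] = (1+ρ)/2.

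| ρ (assumed) | Variance ratio | ANCOVA n per arm if d = 0.85 is on the change SD (t-test on change: 23) | Power at 25 per arm if d = 0.85 is on the follow-up SD: change / ANCOVA |
|---|---|---|---|
| 0.3 | 0.65 | 16 | 0.70 / 0.87 |
| 0.5 | 0.75 | 18 | 0.84 / 0.93 |
| 0.7 | 0.85 | 20 | 0.97 / 0.98 |

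These are linear-model results. They show the direction for skewed counts, not the exact size.

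**3. Simulated overdispersed counts, 25 per arm, unadjusted α = 0.05.** Every count parameter is assumed, and so is a proportional effect.

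*Set-up A: two hospitals, 2,000 runs per scenario.*

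| Scenario | Planned switch | ANCOVA on log counts | Rank ANCOVA |
|---|---|---|---|
| Rate ratio 0.4, baseline mean parameter 2 to 5, weak to moderate tracking | 0.34–0.45 | 0.63–0.75 | 0.59–0.72 |
| Rate ratio 0.4, Spearman about 0.7 | 0.75 | 0.94 | 0.90 |
| Rate ratio 0.5, Spearman about 0.75 | 0.70 | 0.85 | 0.79 |

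Where planned power was already 0.96 or more, the gap nearly vanished.

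*Set-up B: gamma-Poisson counts, mean 6 per month, subject shape 0.8, month shape 3, at least one baseline episode, 1,500 runs.*

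| Rate ratio | Planned | Log-count ANCOVA | Gap (points) |
|---|---|---|---|
| 0.6 | 0.28 | 0.37 | 9 |
| 0.5 | 0.41 | 0.60 | 19 |
| 0.4 | 0.56 | 0.81 | 25 |

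**4. Where the gain comes from.** In a repeat of set-up B at rate ratio 0.5, power was 0.41 as planned, 0.54 for Mann–Whitney on the log change with no covariate, and 0.59 for log-count ANCOVA. The log scale thus supplied 13 of the 18 points. In set-up A with weak tracking, Mann–Whitney on follow-up alone reached 0.67 against 0.34 for the plan, so subtracting a weakly related baseline was itself costly. With strong tracking, follow-up alone fell to 0.60 against 0.75 for change. Conditioning on baseline did well in both cases.

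**5. Rare behaviours.** With a mean of 0.4 per month and rate ratio 0.5, power was 10% as planned against 13% adjusted. Neither analysis is informative there.

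**6. The switch.** In the skewed scenarios of set-up A, Shapiro–Wilk accepted normality in about 1–7% of runs, and power was within 0.01 of Mann–Whitney on change. Null rejection was 0.043–0.064 in set-up A and about 5% in set-up B.

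**The case against.** Most of the opposing case is fair, and it limits the point.

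- **A reader might infer that baseline is ignored.** It is not: it is subtracted, and it also feeds the imputation. The stated primary objective is a comparison of change, and the sizing test is the same Mann–Whitney used as fallback. The plan is coherent; the issue is efficiency.
- **A reader might infer that the normality switch loses power or inflates type I error.** The simulations show neither. Under skewed counts the procedure is in practice Mann–Whitney throughout. What stands is that the data select the test and effect measure.
- **A reader might infer that omitting hospital invalidates the test.** Independent, unblocked Bernoulli draws with the same p in each hospital amount to simple randomisation, so validity does not require the adjustment. Hospital alone adds little power; it is a sensible covariate, not a necessary one.
- **A reader might infer that a rank analysis gives no effect size and cannot be pooled over imputations.** That is too strong. A Hodges–Lehmann shift or probability index with an interval is available, and an index with a standard error can be pooled. The article names none, but such detail commonly sits in a fuller document.
- **The simulated gain depends on assumptions.** A proportional effect favours a log model by construction. This stands, and is why only a range is given. Rank ANCOVA, which does not rely on the log scale, also beat the plan.

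**Conclusion.** The point holds as a recommendation on efficiency and prespecification. The article fixes the method explicitly, so it is a stated choice rather than a detail left to an analysis plan. The unadjusted raw change score is less precise than a baseline-adjusted analysis: the variance ratio is 0.65 to 0.85 for ρ of 0.3 to 0.7 under equal variances. The power loss is roughly 10 to 30 points at rate ratios of 0.6 to 0.4, reaching about 35 in the weakest-tracking scenarios and shrinking to little for rare behaviours or where power is already near 1.

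The direction was the same in every alternative simulated. The size rests on assumed ρ, assumed counts and an assumed proportional effect, none of which the protocol gives, so no single figure should be quoted as the loss. All power figures ignore the planned Bonferroni correction, which would lower power for either analysis.

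**What to change.** Before outcomes are seen:

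1. Prespecify one primary analysis of follow-up frequency adjusted for baseline frequency and hospital. Two suitable forms are ANCOVA on log(count+1) with small-sample or permutation inference, and rank ANCOVA.
2. Report the treatment effect with a 95% CI, pooled over the imputations. If log(count+1) is used, describe the back-transformed effect as a ratio of geometric means of count+1, not as a rate ratio.
3. Drop the Shapiro–Wilk switch, and keep Mann–Whitney on change as a sensitivity analysis.
4. Add a sentence to Sample size saying that the Mann–Whitney calculation now refers to the sensitivity analysis.

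The cost is an amendment to the analysis and sample-size text. No new data or participants are needed, since baseline frequency and hospital are already recorded. The small downside is that the effect is less directly read as a raw change in episodes; descriptive summaries of change by arm can sit beside it.

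### The Mann–Whitney U test is described as a comparison of medians, but for changes in rare, zero-heavy behaviours it can be significant while the two medians are identical

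*Protocol article*

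**What the plan says.** Statistical analysis defines the analysed variable for every participant and follow-up visit: "the difference between the frequency of each suicidal behavior and the baseline frequency will be calculated". If these changes pass a Shapiro–Wilk test, "the mean differences for each behavior between both groups will be compared using the t-Student test". If they do not, "the medians will be compared with the Mann–Whitney U test". The p-values are then Bonferroni-corrected.

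Sample size uses a two-sided 5% level, 80% power and d = 0.85 to reach 25 per group, which it says are needed "to detect a significant difference in the median frequency of self-injurious behaviors with the two tailed Mann–Whitney U test". With 15% loss this becomes 29 per group.

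Neither section states an equal-shape or location-shift assumption, and neither names another effect measure for the rank test.

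**The concern.** The Mann–Whitney test asks whether a randomly chosen participant in one arm tends to have a lower value than one in the other. It becomes a test of medians only when one distribution is the other moved along by a constant. Changes in episode counts are unlikely to behave like that: they are integers, heavily tied, and limited by each participant's baseline.

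If the rule is followed as written, a small p-value will be read as a difference in medians. For a behaviour that most participants do not show, both medians may be zero, and the reported conclusion would then contradict the figures printed beside it. The primary objective is a comparison of change in frequency, so the plan should say which feature of the distribution the test addresses.

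**Working it through.** **1. The plan's own figure.** Inputs from Sample size: two-sided 0.05, power 80%, d = 0.85. I used noncentral-t power with the group size multiplied by the asymptotic relative efficiency (ARE) of the rank test.
- Normal parent, ARE 3/π: 24 per group (power 80.3%; 82.0% at 25).
- Minimum ARE 0.864: 27 per group (power 81.1%; 77.9% at 25).
- Plain t-test: 23 per group.
- Noether's formula, with P = Φ(0.85/√2) = 0.726: n = (1.960 + 0.842)² / [6 × (0.726 − 0.5)²] = 7.85 / 0.307 = 25.6, so 26 per group.

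The stated 25 lies within two of each. For dropout, 25 × 1.15 = 28.75 gives 29 and 25/0.85 = 29.4 gives 30, which is immaterial here.

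**2. When the median wording is right.** If the CALMA distribution is the TAU distribution moved by δ, the differences in mean and in median both equal δ, and d = δ/SD standardises both. Under that model the Sample size sentence is loose but not wrong.

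**3. Why a shift is implausible here.** Change = follow-up − baseline, so it can never be lower than −baseline. A participant at zero cannot improve. Patient eligibility admits anyone with an attempt, a gesture or self-injury, while the analysis takes each behaviour separately. Many participants can therefore start at zero for a given behaviour and show no change.

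**4. Illustrations.** The documents give no frequency distribution, so every input below is assumed. Each row uses 6,000 simulated trials, 25 per arm, two-sided 0.05 without Bonferroni.
- (a) Probabilities of a decrease / no change / an increase are 0.20/0.55/0.25 with TAU and 0.40/0.55/0.05 with CALMA; the size of a change is 1 + Poisson(1).
- (b) Baseline Poisson(0.5); follow-up Poisson(0.5) with TAU and Poisson(0.1) with CALMA.
- (c) As (a), with 0.10/0.45/0.45 against 0.45/0.45/0.10 and size 1 + Poisson(2). This is a deliberately large, opposed effect.
- (d) Rounded normal, mean −1, SD 1 against 4.
- (e) Frequent behaviour: f gamma with shape 0.8 and mean 1; baseline 1 + Poisson(4f); follow-up Poisson(3.5f) against Poisson(1.5f).

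| Case | True medians (TAU, CALMA) | Means | P(TAU change > CALMA), ties half | Rejection | Identical sample medians among significant trials |
|---|---|---|---|---|---|
| a | 0, 0 | 0.1, −0.7 | 0.655 | 56% | 75% |
| b | 0, 0 | 0.0, −0.4 | 0.613 | 31% | 82% |
| c | 0, 0 | 1.06, −1.05 | 0.754 | 94% | 45% |
| d | −1, −1 | −1.0, −1.0 | 0.500 | 8.1% | 1% |
| e | −1, −2 | −1.5, −3.5 | 0.672 | 58% | 2% |

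Case (a) can be checked by hand. The share below zero is 0.20 (TAU) and 0.40 (CALMA); the share at or below zero is 0.75 and 0.95. Both medians are therefore 0. The sign alone decides for CALMA with probability 0.25 × 0.95 + 0.55 × 0.40 = 0.4575. Pairs of equal sign have probability 0.55² + 0.25 × 0.05 + 0.20 × 0.40 = 0.395, and half of them count. The total is 0.4575 + 0.1975 = 0.655.

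Further zero-heavy variants gave rejection of 33 to 65%, with identical sample medians in 74 to 92% of significant trials. Rows (a) and (b), whose inputs are shown, carry the argument.

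**5. A second frequent-behaviour model.** Baseline 1 + Poisson(6 × gamma(1)); follow-up Poisson(baseline × 0.7 × gamma(1.5) scaled to mean 1), multiplied by 0.8 with CALMA. True medians are −2 and −2, and means about −2.1 and −3.1. The test rejects in only about 8 to 10% of trials, and significant trials almost never (about 0.3%) have equal sample medians.

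**6. Is the rank-test branch reached?** Shapiro–Wilk rejected normality in at least one arm in 90% of trials under the model in step 5 and in all trials under (a).

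**The case against.** The strongest reply is that this is loose wording about a valid test. Mann–Whitney remains valid for the null hypothesis of identical distributions. Under the shift model behind a d-based calculation, the mean and median differences coincide. The article prescribes no results sentence. The simulated distributions are assumed and ignore the planned Bonferroni correction, so actual rejection rates would be lower. For frequent behaviours the wording is nearly harmless, as (e) and step 5 show. Most of this stands and limits the point.

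It does not remove the point. The analysis rule states what the test compares, and for zero-heavy behaviours that statement can be false. Bonferroni lowers how often the test rejects, but it does not turn the test into one of medians.

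Some stronger readings are tempting and are not supported:
- **That the sample size is wrong.** It reproduces within about two per group.
- **That the test is invalid.** Even the extreme spread ratio in (d) gives 8.1% rejection, and that case is not the null of identical distributions.
- **That the trial's main conclusion would be wrong.** This depends on distributions the documents do not give, and frequent behaviours show little harm.
- **That new wording would recover a benefit among heavy self-injurers.** In step 5 a saving of about one episode per participant is invisible in the medians, but the rank test also seldom detects it. Rewording keeps the same p-value; only the added mean difference would show the saving.

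**Conclusion.** The point holds as an error in what the test is said to compare. It matters mainly for rarer behaviours analysed one by one, where both medians are likely to be zero. There, under assumed distributions at 25 per arm, the test rejects in roughly 30 to 65% of trials at an unadjusted 0.05, and about 75 to 90% of the significant trials show identical sample medians. Case (c) shows that other assumptions move both figures (94% and 45%). The conclusion rests on the rank-test branch being reached, which is likely for count changes, and on many participants having no change in the behaviour concerned. The Sample size sentence is loose rather than wrong. Neither 25 (29) per group nor the choice of test needs to change.

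**What to change.** In Statistical analysis, replace the statement that medians are compared with a rank-test hypothesis: the probability that change is lower with CALMA than with TAU, counting ties as half, equals 0.5. For each behaviour report:
- that probability with a 95% CI, by a method that allows unequal spread, because case (d) shows the rank-test p-value is only approximate for this hypothesis when spreads differ;
- the between-arm difference in mean change in episodes, with a bootstrap CI.

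In Sample size, either delete the word median or say that d = 0.85 is a standardised shift under an assumed location-shift model.

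The cost is two wording changes and one or two extra estimates from data already collected. No participants, visits or measurements are added.
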